### Data Management

Two separated and secured computers will be used. Patients will be given a specific number characteristic. The respective number-patient relation will be stored on another external hard drive remote from the data computer.

The primary investigator [name] will perform all data analysis. An independent statistician [name] will guide the primary investigator in performing statistics.

### Ethical Considerations

The central and local ethical committees of the University Hospital Antwerp and AZ Monica approved this study (B300201942512; 19/48/559). The present study underlies the principles of the Helsinki Declaration. Only data of patients who gave informed written consent to the project will be considered for analysis. The coding list of target data will be saved in a secured folder on an external hard drive. Only the project leader, study nurse, principal investigator, and second investigator have access to it. Between the members of the research team only coded and deidentified data will be shared.

The research team is committed to full disclosure of the results of the study. The results of the study will be disseminated for research purpose at different conferences and as published articles in peer reviewed journals. Findings will be reported in accordance with international guidelines, and we aim to publish in high impact journals. Given the multitude of outcome parameters, results will be divided over several papers.

## Results

Data collection started in January 2020. In April 2023, the sample size was reached. Data collection will end in April 2025.

Due to the COVID-19 pandemic, the duration to reach the sample size was rather long. Between March 2020 and July 2020, and between October 2020 and December 2020, all nonurgent surgeries were postponed and even consultations were cancelled. Therefore, no new patients could be included, and the follow-up of some patients could not be reassured. An overview of the timeline can be found in Figure 2.

**Figure 2 figure2:**
[figure not shown]
Timeline of study flow.

## Discussion

### Principal Findings

The aim of this study is to investigate which prognostic factors could possibly predict baseline shoulder pain and function, and quality of life, and the evolution of shoulder pain and function, and quality of life in the first 2 years after a total shoulder arthroplasty surgery. A broad spectrum of factors is studied. This is the first longitudinal study to investigate the possible prognostic factors in patients with a shoulder arthroplasty with adequate power. The longitudinal design will allow us to follow patients over 24 months, which makes it possible to analyze and compare the measurements at 6 time points. Only 1 orthopedic surgeon performed the surgeries. This means the surgical technique is not one of the factors that must be taken into account. Parts of the surgery that do differ between patients are taken into account, such as subscapularis handling, and take-down and repair of muscles. The surgery, preoperative screening, postoperative consultation schedule, and everyday practice is the same in each of the included patients. The questionnaires the HSS Shoulder Surgery Expectations Survey and a self-developed questionnaire, adapted from the study of Swarup et al [22] were translated to Dutch for the purpose of this study. Therefore, their validity in the Dutch-speaking population has yet to be established.

As previously mentioned, the amount of shoulder arthroplasty procedures is rising. In contrast with knee and hip arthroplasties, more follow-up consultations with the orthopaedic surgeon are planned with total shoulder arthroplasties. Patients return to regular consultations at the defined timepoints which minimizes the loss to follow-up. Knowledge of potential prognostic factors will have implications toward better rehabilitation strategies of patients after total shoulder arthroplasty**.** With the modifiable potential prognostic factors analyzed, we could change strategies to try and change the outcome. Also, nonmodifiable factors are of interest. We could educate these patients to change or monitor the patient expectations to increase the quality of the outcomes.

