Primary objective: to investigate which potential prognostic factors predict baseline shoulder pain and function measured with Shoulder Pain and Disability Index (SPADI) and the evolution of SPADI in the first 2 years following surgery, in patients with total shoulder arthroplasty.Secondary objective: to investigate which potential prognostic factors predict baseline quality of life measured with Short Form 36 (SF-36) and the evolution of quality of life in the first 2 years following surgery, in patients with total shoulder arthroplasty.

We will study factors such as shoulder function, patient expectations, psychosocial factors, lifestyle factors, sling wear, soft tissue integrity, and physiotherapy treatment.

To reach the aims of this project, a prospective longitudinal study will be carried out over 48 months, starting from January 2020 up to March 2025. The reporting of this protocol is in line with the SPIRIT statement recommendations.

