### Potential Prognostic Factors

Patient characteristics such as body weight and body length, to calculate the BMI. Preoperative shoulder function including shoulder range of motion, shoulder muscle strength, and proprioception of the shoulder before surgery (Tables 1-3).

Soft tissue integrity of the different muscles around the shoulder joint will be collected from the surgeon’s report and from previous surgeries. The shoulder muscles of interest are the rotator cuff muscles, biceps brachii muscles, and triceps brachii muscles. Soft tissue will be scored a 1 if it is damaged either through injury of previous surgery (open or arthroscopic surgery). Soft tissue will be scored 0 if it is not damaged, and no previous surgery has occurred.

Patients’ expectations will be measured with a self-developed questionnaire, based on the HSS Shoulder Surgery Expectations Survey [20]. This survey consists of 17 questions, in Dutch, regarding postoperative expectations of symptom relief, physical function, and psychosocial function. Both spectrum and importance of expectations are measured, in less than 5 minutes. Each question has the following 5 possible responses: “very important,” “somewhat important” “a little important,” “I do not expect this,” and “this does not apply to me.”

Sling wear is also a possible prognostic factor. Patients will be randomized preoperatively in 2 groups with varying immobilization period. Patients in the first group (delayed mobilization group) will be wearing a sling for 6 weeks, the first 4 weeks an abduction sling, followed by 2 weeks of adduction sling. Patients in the second group (early mobilization group) will be wearing an adduction sling for 4 weeks. If a patient cannot be randomized in one of the 2 groups, the patient will be excluded from the study. For example, if a longer immobilization period is needed (complications during surgery, bone grafts used, etc.). Raters will be blinded from the sling wear throughout the whole observation period.

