### Sample Size

Considering a mixed regression model for repeated measures and using a moderate effect size that is still clinically relevant (20 points average decrease in SPADI score), inclusion of 5 covariates, confidence level (α=0.05), and desired power (90 %), the required total sample size is calculated to be 43 participants per group (Edland method, R package longpower 1.0-11) [50-52]. The SD of the SPADI measurements is set at 18, and is estimated from the SD measured in previous studies [31]. The variance of the residuals cannot be estimated from previous studies, but this variance only has a very limited effect on the sample size. It doesn’t change the result of the power calculation and is not included in this analysis. Given the expected dropout rate of approximately 12.5%, a total number of 97 patients will be needed. The power is set at 90% to minimize the chance of making a type II error.

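### The claim of adequate power for the prognostic factors rests on one calculation for two equal groups of 43, which covers neither the observed factors nor baseline SPADI

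*Protocol article*

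**What the plan says.** The primary objective, at the end of the Introduction, is "to investigate which potential prognostic factors predict baseline shoulder pain and function measured with Shoulder Pain and Disability Index (SPADI") and its course over two years. The range of factors is wide: "We will study factors such as shoulder function, patient expectations, psychosocial factors, lifestyle factors, sling wear, soft tissue integrity, and physiotherapy treatment". One of these is allocated. The Potential Prognostic Factors section states that "Sling wear is also a possible prognostic factor" and that "Patients will be randomized preoperatively in 2 groups with varying immobilization period". The rest are observed, and several are scores or physical measurements.

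The Sample Size section holds the one power calculation. The effect is a "20 points average decrease in SPADI score", with SD 18, alpha 0.05, 90% power and "inclusion of 5 covariates". The result is that "the required total sample size is calculated to be 43 participants per group". The groups are not named. No effect size, prevalence or correlation between predictors is given for any observed factor.

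The Discussion (Principal Findings) then states: "This is the first longitudinal study to investigate the possible prognostic factors in patients with a shoulder arthroplasty with adequate power". It does not limit this to any contrast.

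**The concern.** A calculation for two equal groups answers a narrower question than the objective asks. Observed factors need not split evenly, they tend to correlate with each other, and many are not binary. For the same number of patients, an uneven or correlated factor is estimated less precisely than an evenly randomized one.

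The objective also has a part that a sling contrast cannot size at all. The sling is worn after surgery, so it cannot predict preoperative SPADI, and an average decrease in SPADI does not describe a difference at baseline.

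What is at stake is how a null result is read. Under a label of adequate power, a non-significant factor is easily taken as one that does not matter, and the Discussion says that knowledge of these factors should inform rehabilitation strategies.

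**Working it through.** **Inputs.** From the Sample Size section: difference 20 points, SD 18, alpha 0.05, power 90%, 43 per group (86 in total). Assumed here: a two-sided test (sidedness is not stated), the prevalences of binary factors, and the share R² of a factor explained by the other covariates. The calculations are two-sample normal approximations at one time point, with z-sum 1.960 + 1.282 = 3.242.

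**Step 1: the plan's own figure.** n per group = 2 × 3.242² × (18/20)² = 17.02, rounded up to 18. This is not 43. Conversely:
- at SD 18, 43 per group gives 90% power for 18 × 3.242/√21.5 = 12.6 points, a standardized difference of 0.70;
- at 20 points, 43 per group gives exactly 90% power if the SD is 20 × √21.5/3.242 = 28.6.

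The stated inputs and the stated result therefore lead to different answers, and both are carried forward.

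**Step 2: power for a binary factor with 86 patients.** Power = Φ(d × √(n₁n₂/86) − 1.96). Reading A takes 20 points and SD 18 literally, d = 20/18 = 1.11. Reading B takes 43 per group as what 90% power needs, d = 0.70. The third power column is a 10-point difference at SD 18, d = 0.556. The last column is 18 × 3.242/√(n₁n₂/86).

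| Split (n₁/n₂) | A: 20 points, SD 18 | B: d = 0.70 | 10 points, SD 18 | Detectable at 90%, SD 18 |
|---|---|---|---|---|
| 50:50 (43/43) | 99.9% | 90% | 73% | 12.6 points |
| 30:70 (26/60) | 99.7% | 85% | 66% | 13.7 points |
| 20:80 (17/69) | 98% | 73% | 54% | 15.8 points |
| 10:90 (9/77) | 88% | 51% | 35% | 20.6 points |

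Under A, 90% power needs p(1 − p) ≥ (3.242 × 18/20)²/86 = 0.099, so p of about 11% or more.

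**Step 3: correlation with other covariates.** Multiplying n₁n₂/86 by (1 − R²), with R² = 0.3 assumed:
- A: 99% at 50:50, 93% at 20:80, 75% at 10:90;
- B: 77% at 50:50, 58% at 20:80.

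**Step 4: continuous factors.** By Fisher's z, the smallest correlation detectable with 90% power from 86 patients is tanh(3.242/√83) = 0.34, or about 12% of the variance.

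**Step 5: baseline SPADI.** No arithmetic applies. Neither of the readings above comes from a calculation that was set up for a baseline difference.

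**The case against.** Several points on the other side stand.

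- Sling wear is itself a listed prognostic factor, so the calculation does fit part of the objective. That the two groups are the sling arms is an inference: no other pair of groups appears in the article, but the Sample Size section does not say so. Nor does it say that the 20 points are a between-group difference.
- On the stated 20 points and SD 18, power is ample for most plausible splits. A reader might infer that the design lacks adequate power for prognostic factors. The documents do not support that: on their own inputs, a factor with 20% prevalence has 98% power, and 93% with R² = 0.3.
- A reader might also infer a 25–50% chance of missing an effect of the planned size. For splits between 20:80 and 10:90 that range holds only under reading B. Under reading A the chance is about 2% at 20:80 and 12% at 10:90.
- The planned analysis is a mixed model over six visits. The approximations here ignore the repeated measures and any residual variance that prognostic covariates remove.
- Scales such as catastrophizing and self-efficacy are not said to be dichotomized, so the table of splits does not apply to them.
- No section says that a non-significant factor will be declared irrelevant. That harm is a risk of interpretation and not a stated plan.

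These points limit the size of the finding but do not justify the sentence in the Discussion. Reading A shows adequacy only for large differences and is not consistent with 43 per group. Reading B accepts 43 per group and shows lower power for uneven factors. Neither covers baseline SPADI.

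**Conclusion.** The point holds in a limited form: adequate power is not demonstrated for the prognostic factors in general. It is shown, at most, for one contrast of two equal groups. This is an affirmative statement that the article's own calculation does not support, so it is not a matter of detail left to another document.

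Whether there is a real shortfall, and how large, cannot be settled until 43 per group is reconciled with 20 points and SD 18. If the inputs are right, the shortfall is confined to factors rarer than about 11%, strongly correlated factors, and effects well below 20 points. If 43 per group is right, it begins at moderate imbalance, with about 85% power at 30:70. These figures rest on assumed prevalences, an assumed R², a two-sided test and a two-sample approximation.

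**What to change.** 1. **Sample Size section.** Reconcile 43 per group with the stated 20 points and SD 18. Then name the contrast that was sized and say that it compares two equal groups.
2. **Discussion, Principal Findings.** Remove the power claim for the prognostic factors in general, or limit it to that contrast. In its place, give approximate differences detectable with 90% power from 86 patients at SD 18: about 12.6 points at 50:50, 13.7 at 30:70, 15.8 at 20:80 and 20.6 at 10:90, unadjusted, and a correlation of about 0.34 for continuous factors. Label them as two-sample approximations, and update them if the reconciliation changes the SD.
3. **Interpretation.** Add that a non-significant factor is not evidence of no prognostic value unless its 95% confidence interval excludes a clinically relevant difference.

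The cost is wording and one small table. Recruitment is complete, and no patients, visits or measurements are added. The one downside is a less favourable power statement.

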## Appendix

Multimedia Appendix 1 Informed consent.

Multimedia Appendix 2 Visual representation of the ordinal scale for functional internal rotation.

Multimedia Appendix 3 Visual representation of the ordinal scale for functional external rotation.

## Abbreviations

CS: Constant and Murley Score
HHD: handheld dynamometer
SPADI: Shoulder Pain and Disability Index
SF-36: Short-Form 36
VAS: Visual Analogue Scale
